# 1. INTRODUCTION

## 1.1 BACKGROUND

Conventional and dedifferentiated chondrosarcoma is the second most common primary bone tumour with an incidence of approximately 1/200,000 individuals/year. There are approximately 110 newly diagnosed chondrosarcomas annually in the UK (Whelan *et al*). There is evidence that the majority of these tumours arise from an enchondroma – a benign cartilaginous tumour. Chondrosarcoma are typically resistant to chemotherapy and radiotherapy and the overall survival rate has not changed in 30 years.

Clinical management decisions for patients with cartilage tumours are based on a combination of the tumour grade determined by a histopathologist based on its appearance down the microscope, and clinical evaluation – mainly imaging, and pain. Histological tumour grade (G) is the best prognosticator of metastatic disease and survival (apart from when the lesions occur in the phalanges as these have a negligible risk of metastasis). Broadly speaking, enchondroma and chondrosarcoma GI (low grade tumours) have an excellent prognosis and can be treated by curettage (scraping out the tumour from the bone). However approximately 15% of low grade cartilaginous tumour recur with some showing a high grade component at the time of recurrence (*Schawb et al; Ma et al*).

Chondrosarcoma GII and GIII (high grade disease) disease is generally treated with wide local excision and has a significantly higher risk of local recurrence and metastatic disease than enchondromas and GI tumours. However, the figures for survival vary between GII and GIII tumours: the 5 and 10 year survival rate of GII is 81% and 64%, and GIII is 43% and 29% respectively (*Fiorenza et al*). Patients who survive for 10 years are more likely to die from another disease.

Approximately 10% of conventional chondrosarcoma transform into a non-conventional variant known as dedifferentiated chondrosarcoma which are associated with a very poor 10% 5 year survival (*Bindiganavile et al*).

The variability in clinical outcome associated with grade is likely to be accounted for, at least in part, by the inter-observer variability between cellular pathologists in grading chondrosarcomas (*Eefting et al*). These challenges impact on clinical management of patients.

**Recent developments**

We were the first to show that *IDH1* mutations are detected in ~60% of conventional central chondrosarcomas and enchondromas (Amary *et al*). It is now known that the presence of *IDH1* mutations in the tumour neither affects the prognosis nor the clinical management of the patient.

We then investigated in a proof of concept study (in press Cancer Medicine) involving 30 patients if *IDH1* mutations can also be found in the blood , that is, as circulating tumour DNA (ctDNA). We found that 14 patients with GIII and dedifferentiated chondrosarcoma, and 50% of patients with GII chondrosarcoma (7 out of 14 patients) had measurable levels of mutant copies in their blood. Of note is that no circulating tumour DNA was identified in the blood of 8 patients with either an enchondroma or GI chondrosarcoma.

Based on our results **we hypothesise** that the detection of mutant *IDH1* in the blood is a more sensitive prognostic indicator for chondrosarcoma than histology.

## 1.2 RATIONALE FOR CURRENT STUDY

- Approximately 60% of central cartilaginous tumours have an *IDH1* mutation.
- Currently the most accurate prognostic indicator is the tumour grade (high and low grade), which is provided by the histopatholoists.
- Up to now treatment of cartilaginous tumours is largely based on histology: low and high grade tumours are treated differently with the latter being treated more radically and with greater morbidity.
- It is recognised that there is a lack of consistency and reproducibility between pathologists distinguishing between high and low grade cartilaginous tumours.
- We have preliminary evidence that we can detect ctDNA in the blood of patients with the high grade (GIII) cartilaginous, and in approximately 50% of patients with GII tumours but not in low grade cartilaginous tumours.
- Our preliminary data indicate that detection of pre-surgical ctDNA (mutant *IDH1*) is a more reproducible and accurate prognostic indicator of tumour behaviour than tumour grading.
- A blood test which could be taken at a GP surgery for monitoring patients for relapse rather than imaging at a hospital would be better for patients and it would be more cost-effective, efficient than what is currently offered.

# 2. STUDY OBJECTIVES

## 2.1 PRIMARY AIM

1. We aim to provide a more accurate and highly reproducible prognosis for patients with chondrosarcoma by evaluating a biomarker which is present in the majority of conventional central cartilaginous tumours (enchondroma and chondrosarcoma).

PRIMARY OBJECTIVES

1. Does detection of pre-operative ctDNA indicate a poorer prognosis than if not detected?
2. Does detection of post-surgery ctDNA predict tumour relapse?
3. Does ctDNA detection after surgery indicate residual and or metastatic disease?

iii) Can ctDNA in conjunction with imaging allow diagnosis of chondrosarcoma without a biopsy?

iv) Can correlation of ctDNA with histology reduce the variation in grading of cartilaginous tumours provided by histopathologists?

v) Can correlation of ctDNA with imaging reduce the variation in grading of cartilaginous tumours provided by radiologists?

### 2.2 SECONDARY OBJECTIVE/S

1. Establish a UK-wide collaborative clinical research network for chondrosarcoma, a disease in which neither clinical trials nor new treatments are available.
2. Samples will be stored for future investigation for other biomarkers while development of tests in other cancers is optimized.

# 3. STUDY METHODOLOGY

## 3.1 OVERALL DESIGN

We will recruit a minimum of 100 patients newly diagnosed with central chondrosarcoma, and 30 patients with benign cartilaginous tumours (enchondroma). Patients will be requested to give a small sample of blood before surgery and at their follow-up routine hospital appointments for up to a minimum of 12 months. In other respects patients will receive standard of care for their tumour.

- All equipment used in this study is serviced annually as required by UKAS standards
- All tests are performed according to the standard operating procedures in the clinical / diagnostic department which is a UKAS-accredited laboratory.
- All staff are trained in the process and signed as being capable of doing the work before being allowed to undertake this work.

**Blood samples**

20 ml of blood is taken by venepuncture prior to surgery and when the patient attends their routine follow up appointments and if they attend at other times.

- The blood sample is put into 2 DNA-stabilising tubes which will be supplied by the Sponsor site.
- The blood samples, which are stable for up to 1 week at room temperature, will be sent in stamped addressed packages employing the appropriate safety standards to the sponsor site for processing.
- The blood will be dispatched within 72 hours of being taken from the patient.
- The blood sample **must not be placed** in the fridge or freezer if in a DNA-stabilising tube.
- Receipt of the blood sample is logged by the research/study team and it is processed immediately according to standard operating procedures.
- The plasma and blood cells are frozen in a -800C freezer. The temperature of the freezer is monitored and is alarmed is there is a drop in temperature.

[figure not shown]

**Tumour samples**

The tumour biopsy and resection sample will be processed in the usual manner at each site and formal-fixed paraffin-embedded (FFPE) tissue will be produced. If there is tumour tissue which is surplus to diagnostic requirement it will be frozen and biobanked for future research projects at the hospital where the surgery takes place. The FFPE tissue treated in the normal manner and histology tissue sections are given to the histopathologist for a tissue diagnosis to be made. The result is discussed at the routine MDT meeting. Following the MDT meeting the tissue block is sent to the sponsor site (RNOH). The ‘sender’ site informs the sponsor site by secure email that the material has been despatched; on receipt of the material at the sponsor site, the research/study team informs the ‘sender’ of the sample arrival.

The sample with the required details is logged onto the study database (excel file) – see below.

The sponsor site cuts a tissue section, reviews the histopathology and then undertakes DNA extraction. The DNA will then be assessed for the presence of mutant *IDH1*. If an *IDH1* mutation is detected in the tumour, the plasma samples taken before and longitudinally after treatment will be tested for evidence of the mutant *IDH1*. In those patients whose tumours the *IDH1* mutation is not detected, ctDNA samples will be stored for future studies currently being developed.

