## 3.5 RECRUITMENT AND METHODLOGICAL PROCESS

**Recruitment**

- A tissue diagnosis of enchondroma/chondrosarcoma will be made by a consultant pathologist.
- Cases are discussed at the MDT meeting where the diagnosis is confirmed and the patient is identified as a possible candidates for the study. The MDT co-ordinator will then inform the research /study team (eg. Biobank staff or research nurses) about the eligible patients via secured email (nhs.net or trust intranet).
- The research/study team will make arrangements to approach the patient at the next routine hospital appointment (diagnosis appointment) to introduce him/her to the study and give the PIS.
- Consent to enter the study will be sought from each participant only after a full explanation about the study has been given, an information leaflet offered and time allowed for consideration.
- Consent is sought at a pre-op assessment appointment or prior to surgery at which time the first blood sample could be taken; alternatively the blood sample could be taken when the patient is under anaesthetic prior to the start of the operation.
  - - The Patient has the opportunity to decline consent. The consent form will be countersigned by the study/research team member; a copy of the signed form is given to the patient for their records.
- The research/study team will allocate the patients with a unique patient-ID (see below) on a password protected excel file (each participant site will have their own specific file).
- A blood sample will be obtained at each patient’s routine follow up hospital appointments for up to a minimum of 12 months or for the duration of the study (range 12 - 36 months).
- If routine appointments are not within 3 months, a letter will be sent to the patient for the attention of their GP surgery where patients may have their blood sample taken and sent to the sponsor site.

All members of the research/study teams will be trained in obtaining informed consent, safeguarding adults and research and information governance. The recruitment process will be the same across

all 5 sites.

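### Objective iii (diagnosis without a biopsy) gets ctDNA results only from patients whose tissue already shows an IDH1 mutation, and the plan does not say how the rest enter its accuracy estimates

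*Protocol*

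**What the plan says.** Section 2.1 of the protocol lists, under the primary objectives, item iii: "Can ctDNA in conjunction with imaging allow diagnosis of chondrosarcoma without a biopsy".

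The Tumour samples part of Section 3.1 sets the laboratory rule. The sponsor site reviews the histopathology, extracts tumour DNA and tests it for mutant IDH1. Plasma is assayed only if a "mutation is detected in the tumour, the plasma samples taken before and longitudinally after treatment will be tested for evidence of the mutant" gene. For patients in whose tumours the IDH1 "mutation is not detected, ctDNA samples will be stored for future studies currently being developed".

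Section 1.2 gives the share affected: "Approximately 60% of central cartilaginous tumours have an" IDH1 mutation. Section 3.1 plans at least 100 chondrosarcoma and 30 enchondroma patients.

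Section 3.5 (Recruitment) starts from tissue: "A tissue diagnosis of enchondroma/chondrosarcoma will be made by a consultant pathologist". The inclusion criteria in Section 3.4 also admit patients on imaging alone.

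Section 7 plans a logistic regression with diagnosis as the outcome and ctDNA level as a continuous predictor. It does not say whether patients without an assayed plasma sample count as negative or are left out.

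**The concern.** A test proposed as a substitute for biopsy would be used in patients whose tumour genotype is unknown. Using tissue as the reference standard in the study is proper. The difficulty is that the tissue result also decides who receives the index test, so no ctDNA result is generated for about 40% of patients.

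Two things are at stake. First, sensitivity estimated in assayed patients is conditional on a tissue-proven mutation, yet objective iii invites the reader to apply it where no tissue exists. Secondly, the wild-type patients, in whom any IDH1 signal would be an assay error, contribute no observed false-positive rate, and fewer benign patients than are recruited contribute to specificity. An analysis plan can choose the denominator but cannot supply results that were never generated.

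**Working it through.** **Inputs from the protocol.** Mutation prevalence p about 0.60 (Section 1.2). 100 chondrosarcomas and 30 enchondromas (Section 3.1). Under Measurement of IDH1 mutation: background error of 1 mutant-only droplet per about 18,000, an average of 1,489 molecules per time point, positivity at 2 or more mutant-only droplets, and 7 variant assays.

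**Assumptions.** p is the same in chondrosarcoma and enchondroma (0.50 to 0.70 shown). The sensitivities of 50%, 75% and 100% below are illustrative.

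**The protocol's own figure.** Pilot detection in grade II tumours is "7 out of 14 patients": 7/14 = 50%, exact 95% interval 23% to 77%. It reproduces.

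**Who is assayed**
- p = 0.60: 60 chondrosarcomas + 18 enchondromas = 78 of 130. Not assayed: 40 + 12 = 52.
- p = 0.50: 50 + 15 = 65 assayed.
- p = 0.70: 70 + 21 = 91 assayed.

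**Sensitivity.** With wild-type patients counted as negative, all-patient sensitivity = p × s, where s is the sensitivity in assayed patients.

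| s in assayed patients | p = 0.50 | p = 0.60 | p = 0.70 |
|---|---|---|---|
| 50% | 25% | 30% | 35% |
| 75% | 37.5% | 45% | 52.5% |
| 100% | 50% | 60% | 70% |

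The overstatement from using assayed patients only is 1/p: 2.0, 1.67 and 1.43. As counts at p = 0.60, 45 positives give 45/60 = 75% (95% interval 62% to 85%) among those assayed, but 45/100 = 45% (35% to 55%) among all.

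**Is counting wild-type patients as negative accurate?** Expected background droplets are 1,489/18,000 = 0.0827. The Poisson probability of 2 or more is 1 − e^(−0.0827) × (1 + 0.0827) = 0.32% for one assay. For seven assays, assumed independent, it is 1 − (1 − 0.0032)^7 = 2.2%. The error in all-patient sensitivity is (1 − p) times this: 0.4 × 0.32% = 0.13 points, or 0.4 × 2.2% = 0.9 points. Even with s = 100%, all-patient sensitivity is therefore 60.1% to 60.9%.

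**Specificity.** With no positives among n assayed benign patients, the exact upper 95% limit on the false-positive rate is 1 − 0.025^(1/n).
- n = 18: 18.5%
- n = 30: 11.6%

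The second limit is earned only if all 30 are assayed. Counting 12 unassayed enchondromas as negative enlarges the denominator without adding observations.

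**The case against.** A reader might infer that objective iii cannot be answered, or that wild-type patients vanish from the study. The documents do not support this. These patients are enrolled, their tumours are genotyped and their plasma is stored. An IDH1 assay should be negative when the tumour lacks the mutation, and counting them so recovers all-patient sensitivity to within about 1 percentage point on the protocol's own error rate. This stands.

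A reader might also infer that an inflated sensitivity will be reported. Section 7 neither says so nor rules it out, and the analysis population is commonly left to an analysis plan, which is not at hand. The inflation is conditional on the denominator. However, unassayed patients have no measured ctDNA level and would fall out of the regression unless the plan assigns them one.

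Nor would every wild-type patient necessarily be a missed diagnosis. Objective iii combines ctDNA with imaging, and the protocol does not describe what would follow a negative ctDNA result. The figures here concern ctDNA alone.

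Grade-specific figures are tempting but unsupported. They need an assumed grade mix, and a pilot limited to mutant tumours, which Section 1.1 does not state. Read as separate groups, the pilot counts also sum to 14 + 14 + 8 = 36 against 30 patients stated. The 1/p ratio needs none of this.

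On specificity, mutant enchondromas are the benign tumours that could shed mutant IDH1, so the more demanding cases are assayed. The gain from 18.5% to 11.6% would come largely from expected negatives.

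Finally, the tissue gate is reasonable for the prognosis and relapse objectives. The conflict is confined to objective iii.

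**Conclusion.** The concern holds in a limited form. As planned, objective iii yields ctDNA results only for patients already known from tissue to be IDH1-mutant, about 78 of 130. If accuracy is estimated in those patients alone, ctDNA sensitivity is overstated about 1.67-fold for a setting without tissue (1.43 to 2.0 at 70% to 50% prevalence). All-patient ctDNA sensitivity cannot much exceed 60%. The false-positive rate in wild-type patients is modelled at 0.32% to 2.2% but not observed.

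This rests on the 60% prevalence applying to both tumour groups, on the stated assay error rate and, for the seven-assay figure, on independence. The specificity limits assume no benign positives. The severity is should-fix: the objective sits under the primary heading and bears on omitting biopsy, but the defect can be corrected with data and samples the study already collects.

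**What to change.** For objective iii, do one of the following.

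1. Keep all enrolled patients in the denominator and count tissue-wild-type patients as ctDNA-negative. Report all-patient sensitivity and specificity first and mutant-only figures second. Label the wild-type negatives as assigned rather than observed, and state how patients without a tissue genotype are handled. This costs only text; the headline sensitivity will be lower.
2. Restrict objective iii to patients with a tissue-proven IDH1 mutation and drop the reference to avoiding biopsy. This also costs only text, but narrows the claim.

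Optionally, assay the stored pre-operative plasma of the roughly 52 wild-type patients, masked to genotype and diagnosis, so that the false-positive rate is measured. No new patient or blood draw is needed. Without the genotype, however, the laboratory does not know which variant assay applies, so up to 7 assays per sample may be needed. Masking everyone extends this to about 130 samples. Plasma held for future biomarker work would be used up.

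Keep the tissue gate for the prognosis and relapse objectives and for the serial post-operative samples.

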**Measurement of IDH1 mutation**

Droplet digital polymerase chain reaction (ddPCR) is currently the most sensitive and accurate method for detecting and quantifying mutant DNA molecules. We will use the BioRad QX200 ddPCR platform for this study as using this machine we have demonstrated that we can detect the common *IDH1* mutations at below 1 mutant molecule in 10,000 wildtype molecules and quantify mutant molecules across over 4 orders of magnitude (Cancer Medicine in press). We have also optimized the ddPCR assays for the 7 common *IDH1* variants in both formalin-fixed paraffin-embedded tumour and blood samples.

Based on the background error rate of the assay (1 mutant only droplet per ~18,000 wild type droplets), and the average number of molecules we assessed per time point (n=1489), blood samples were deemed to be circulating tumour DNA (ctDNA)-positive if they had a minimum of 2 mutant only droplets.

This process is set up as a standard NHS clinical service with standard operating procedures in an UKAS-accredited histopathology department.

The equipment is serviced annually.

**Data Analysis**

The ctDNA level in the blood pre and post-surgery will be correlated with the tumour size, anatomical site, clinical outcome (symptoms, imaging for metastasis and local recurrence).

**Pathology and Radiology Review**

At least one representative pathologist and radiologist from each of the 5 different units will meet once every 9 months to review the pathology and radiology respectively from all patients. At least one representative surgeon from each of the 5 units will present their opinion as to the treatment that they would undertake. The opinions will be logged. At the end of the 36 months a meeting will take place to review all of the cases. This will improve the criteria employed for grading chondrosarcoma across the UK bone sarcoma centres.

## 3.2 setting and timescale

The patients will be recruited when they are being treated for a cartilaginous tumour in one of the 5 bone tumour units in England (Royal National Orthopaedic Hospital, Stanmore; Royal Orthopaedic Hospital Birmingham; Nuffield Orthopaedic Hospital, Oxford; Robert Jones and Agnes Hunt NHS Trust, Oswestry; and the Freeman Hospital Newcastle Upon Tyne.

Participants will be recruited from the start of the project for a 24-month period. All patients will be followed for a minimum period of 12 months. Hence the study will close at 36 months after its initiation.

| **Research Task** | **Time Points** | | | | |
| --- | --- | --- | --- | --- | --- |
|  | Appointment when patient given their diagnosis following biopsy and MDT meeting | Pre-op assessment | Surgery | 1st post- op assessment (6 weeks after surgery) | Post–op assessments - national guidelines |
| Approach patients for participation (PIS given) |  |  |  |  |  |
| Consent obtained |  |  |  |  |  |
| Pre-op blood sample taken |  |  |  |  |  |
| Tissue obtained |  |  |  |  |  |
| Post-op blood sample obtained |  |  |  |  |  |
| Serial blood samples intervals at clinical appointments  or at GP surgery approximately every 3 months. Study ends at 36 months. |  |  |  |  |  |

Pre-op = before the operation/surgery

Post-OP = after the operation/surgery

BX = biopsy

## 3.3 Study outcome measurements

1. Detection of *IDH1* ctDNA pre-operatively
2. Levels of the *IDH1* ctDNA after surgery
3. Correlation of ctDNA levels with histology, radiology and clinical behaviour of tumour

## 3.4 PARTICIPANTS

**Groups**

In this study we will prospectively recruit a minimum of 100 patients newly diagnosed with chondrosarcoma and 30 patients with cartilaginous tumours (enchondroma – benign cartilage tumours).

**Inclusion criteria**

All patients 16 and above with a tissue and/or an imaging diagnosis of conventional and dedifferentiated chondrosarcoma, enchondroma, and atypical cartilaginous tumours (WHO criteria) identified at the bone tumour MDT meetings will be invited to participate in the study.

**Exclusion criteria**

Participants may not enter the study if any of the following apply;

- Prisoners
- Non-NHS patients
- Patients who are not capable of understanding the study
- Patients who are needle-phobic
- Patients who decline
- Patients know to hepatitis B or C positive; patients with HIV infection.

## 3.5 RECRUITMENT AND METHODLOGICAL PROCESS

**Recruitment**

- A tissue diagnosis of enchondroma/chondrosarcoma will be made by a consultant pathologist.
- Cases are discussed at the MDT meeting where the diagnosis is confirmed and the patient is identified as a possible candidates for the study. The MDT co-ordinator will then inform the research /study team (eg. Biobank staff or research nurses) about the eligible patients via secured email (nhs.net or trust intranet).
- The research/study team will make arrangements to approach the patient at the next routine hospital appointment (diagnosis appointment) to introduce him/her to the study and give the PIS.
- Consent to enter the study will be sought from each participant only after a full explanation about the study has been given, an information leaflet offered and time allowed for consideration.
- Consent is sought at a pre-op assessment appointment or prior to surgery at which time the first blood sample could be taken; alternatively the blood sample could be taken when the patient is under anaesthetic prior to the start of the operation.
  - - The Patient has the opportunity to decline consent. The consent form will be countersigned by the study/research team member; a copy of the signed form is given to the patient for their records.
- The research/study team will allocate the patients with a unique patient-ID (see below) on a password protected excel file (each participant site will have their own specific file).
- A blood sample will be obtained at each patient’s routine follow up hospital appointments for up to a minimum of 12 months or for the duration of the study (range 12 - 36 months).
- If routine appointments are not within 3 months, a letter will be sent to the patient for the attention of their GP surgery where patients may have their blood sample taken and sent to the sponsor site.

All members of the research/study teams will be trained in obtaining informed consent, safeguarding adults and research and information governance. The recruitment process will be the same across

all 5 sites.

